### SMS drinking assessments without feedback (SA)

Individuals in the SA group will not receive any pre-weekend assessments but will receive identical post-weekend SMS drinking assessments to the intervention group at 12 pm on Sunday for 12 weeks. Upon receiving their responses, the computer will send the following text message: ‘Your response has been received and is appreciated.’ This group is critical to separate the effect of the intervention from that associated with assessment reactivity [38].

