### Control

Individuals in the control group will not receive any SMS drinking assessments.

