### Follow-up measures

Follow-up data will be obtained through a password-protected website at three-, six- and nine-months after ED discharge. At each time point, alcohol consumption data in the last 30 days will be collected using the TLFB procedure. Alcohol-related injuries are measured using the IBC, drug use measured using the ASSIST, depression and anxiety using the PHQ-4, and drinking norms and behavioral control through identical questions to baseline. At nine-month follow-up, all participants will complete a structured diagnostic assessment for determining Diagnostic and Statistical Manual of Mental Disorders, 4th Edition (DSM-IV) diagnoses for alcohol abuse and dependence. Individuals who meet alcohol abuse or dependence criteria will also receive alcohol treatment referrals.

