If the intervention does result in significantly lower rates of alcohol use and/or alcohol-related adverse consequences, analyses will be conducted separately to determine whether these effects are mediated by pre-weekend drinking intention and SMS goal-setting patterns. For a variable to be a mediator (a) intervention condition must be significantly related to the intermediate variable; (b) the intermediate variable must be significantly related to alcohol outcome; (c) intervention condition must be significantly related to alcohol outcome; and (d) after controlling for the intermediate variable, the relationship between intervention condition and outcome is significantly reduced. Product of coefficients methods will be used to determine the size and significance of the reduction in the effect of intervention due to inclusion of the mediators. We will also conduct exploratory analyses of potential moderators of the intervention. We will be able to explore whether baseline ED presentation attributable to alcohol and drug use is an important moderator of change in drinking behaviors in addition to the demographic moderators. These will be completed with another set of multivariable regression models. All analyses will be performed with two-sided *P* values considered significant when below 0.05.

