## Discussion

The TRAC study is the first large-scale randomized trial to examine the effectiveness of a text message program for initiating and maintaining reductions in binge drinking among at-risk young adults. If found to be effective, our intervention could be easily scaled-up as a stand-alone program to provide widespread support with minimal disruption to normal clinical practice. Additionally, it could easily be included as a piece in a multi-component intervention, such as a “booster” to traditional in-person counseling interventions. By incorporating longitudinal assessments of drinking behavior in a patient’s natural environment through SMS, stepped-care models could be built where individuals who continue to report hazardous use after program exposure could then be referred directly to a help line or counselor.

There are several potential strengths of our research design worth mentioning. In addition to being large enough to demonstrate reductions in alcohol consumption immediately following intervention (three-month follow-up) as well six months later (nine-month follow-up), we have sufficient power to examine mediators of change associated with this intervention. Inclusion of an assessment-only group minimizes the potential for assessment effects to bias estimates of intervention efficacy. While all participants complete informed consent, where we outline the various treatments they may be subjected to, we do not specifically tell them which one. We believe that this may reduce expectation biases. All baseline measures and outcomes are reported to an automated computer system, potentially increase disclosure of potentially sensitive or embarrassing information, thus reducing reporting biases. By collecting pre-weekend drinking intentions/plans, goal-setting/plan changes, and post-weekend consumption in the intervention group, we will be able to examine “micro processes” or mechanisms of change not previously available in brief intervention studies. Finally, we have made efforts to design our mobile intervention both from a theory-driven approach to behavior change [44] and a user-centered approach [45], which will serve the dual purposes of increasing potential effectiveness as well as reducing intervention attrition.

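### The between-arm mediation test is set on two variables collected only in the SA+F arm: it is not estimable for pre-weekend intention and uninformative for SMS goal-setting

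*Protocol article*

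**What the plan says.** All references are to the protocol article.

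**The test.** The Statistical analysis section plans, if the intervention shows a significant benefit, separate analyses of "whether these effects are mediated by pre-weekend drinking intention and SMS goal-setting patterns". It sets four conditions. The first is that "intervention condition must be significantly related to the intermediate variable". The second and third require the mediator and the condition each to be related to the alcohol outcome. The fourth is that "after controlling for the intermediate variable, the relationship between intervention condition and outcome is significantly reduced". A product of coefficients is to give the size and significance of that reduction. The Outcomes section names the same two variables as processes mediating the intervention's influence on drinking.

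**The data.** The SA+F intervention section describes a Thursday dialog that asks about weekend drinking plans and, after two affirmative replies, about setting a goal. For the assessment-only arm, "Individuals in the SA group will not receive any pre-weekend assessments". For the third arm, "Individuals in the control group will not receive any SMS drinking assessments". Follow-up measures lists consumption, injuries, drug use, depression and anxiety, and "drinking norms and behavioral control through identical questions to baseline". Neither intention nor goal-setting is on that list, nor among the baseline measures.

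**The claims.** The Abstract, Background and Discussion say that intention data come from the intervention group. Randomization justifies the 2:1:1 ratio by mechanism analyses within that group. The Discussion adds that "we have sufficient power to examine mediators of change associated with this intervention".

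**The concern.** Mediation of a randomised effect is a statement about a contrast between arms: how far the intervention moves the mediator relative to a comparator, and how much of the outcome difference goes with that movement. It needs the mediator in at least two arms. Here it is collected in one.

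At stake is what the trial can say about how the program works. A team that follows the text literally would find no estimate for intention. For goal-setting it could obtain one by a coding choice that makes the answer look positive whatever the truth. The power claim also tells readers that a test is well supported when, for the two mediators named, it has no valid form.

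**Working it through.** The plan gives no figure on this point to reproduce. The Sample size section covers only the difference in binge drinking days between intervention and control. The check is therefore whether the planned quantities can be estimated.

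**1. Where each variable is collected**

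| Variable | SA+F | SA | Control |
|---|---|---|---|
| Pre-weekend intention | Thursday text | not asked | not asked |
| SMS goal-setting | Thursday text, after two affirmative replies | does not occur | does not occur |
| Norms and behavioral control items | web | web | web |
| Binge drinking days (outcome) | web | web | web |

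With 750 participants at 2:1:1, SA+F has 750 × 2/4 = 375. SA and control have 750 × 1/4 = 187.5 each, together 375. So half the trial has no value of either mediator. This follows from the design and not from dropout, so imputation has no comparator information to draw on.

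**2. Intention**

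Let T be condition (1 = SA+F, 0 = comparator), M the mediator and Y the outcome. In linear form the planned analysis needs:

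- M = i + aT + error (path a, the first condition)
- Y = j + c′T + bM + error (the fourth condition, and path b)
- indirect effect = a × b

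On every row where M is observed, T = 1. The columns for the intercept and T are then identical, and the matrix [1, T] has rank 1 of 2 (confirmed numerically on 375 rows). Hence a is not identified, c′ cannot be separated from the intercept, and a × b has no value. Only b, the association within SA+F, can be estimated. Of the four conditions, the second can be examined within SA+F and the third across arms; the first and fourth cannot be examined at all. Coding comparators as zero is no way out, because those participants do have weekend intentions. They were simply not asked.

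**3. Goal-setting, with comparators coded zero**

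This variable is part of the intervention, so zero can be defended as a description of the other arms. Least squares then gives:

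- a = mean goal-setting in SA+F − 0, which is positive as soon as anyone in SA+F sets a goal
- b = the slope of Y on M within SA+F alone, since M does not vary elsewhere
- c′ = total arm effect − a × b

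The first condition is met by construction. The apparent reduction in the arm effect is the within-SA+F slope multiplied by the mean goal-setting rate. Randomisation adds nothing to it: people who accept goals may differ from those who decline.

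**4. Illustration**

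In 500 simulated trials with 262 SA+F and 131 control participants (about 375 × 0.7 and 187.5 × 0.7, using the plan's 30% attrition), neither the intervention nor goal-setting had any true effect. An assumed personal propensity drove both goal-setting and change in drinking (coefficient −2.0, residual SD 4). Path a was significant in 100% of trials, and so was the Sobel test of the product. The 100% depends on the assumed strength of that propensity and is not a property of this trial. The plan would also usually have stopped such trials earlier, because it first requires a significant arm effect. The simulation shows only that the product-of-coefficients step cannot tell mediation from self-selection under this coding.

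**The case against.** Four arguments can be made for the plan.

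- **The analysis is secondary and conditional.** It runs only after a significant benefit. The primary outcome, the main secondary outcome, the sample size, the estimating-equation models and the intention-to-treat comparison do not depend on it. This stands and limits the severity.
- **The mechanism aim is mostly worded within the arm.** The Abstract, Background, Randomization and Discussion all speak of the intervention group. An analysis running from intention to goal to the following Sunday report is feasible with the planned data. This also stands. A reader might infer that the trial can say nothing about mechanism, or that the 2:1:1 ratio has lost its justification. The documents do not support either: Randomization rests the ratio on within-group analyses, and those can be done.
- **Goal-setting is absent by nature in the comparators, so a model can be fitted.** This is correct. A reader might infer that neither mediator allows any computation. That holds for intention only; for goal-setting the fault is that the result carries no information on mediation.
- **A separate analysis plan may settle it.** This does not stand. The article does not leave a detail open. It states a specific test and a data collection that rules the test out, and an analysis plan could resolve this only by changing the test or its variables.

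A reader might also infer that a within-arm correlation is going to be reported as mediation. The article does not say so, and its own first condition would have to be met before a variable counted as a mediator.

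**Conclusion.** The point holds in this form: Outcomes and Statistical analysis attach a between-arm mediation test to variables collected in one of three arms. For intention, the condition-to-mediator path, the mediator-adjusted condition effect and the product of coefficients are not estimable. For goal-setting, they can be computed only by coding about 375 of 750 participants as zero, and the test is then uninformative. The power of the test as stated is undefined for intention and without meaning for goal-setting, so the Discussion's claim has no basis for these two mediators.

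This rests on the article's lists of baseline and follow-up measures being complete for intention and goal-setting. Its statements that these data come from the intervention group support that reading. No assumption about effect size is needed; only the illustration uses one.

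It should be fixed, because it changes what the trial can conclude about mechanism. It is not critical: no efficacy conclusion depends on it.

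**What to change.** 1. **Outcomes and Statistical analysis.** Replace the between-arm mediation test of intention and goal-setting with a within-SA+F process analysis relating each week's intention or goal to the following Sunday report. State that the result is a non-randomised association and makes no claim to mediate the arm effect. Since the goal question is reached only after two affirmative replies, say in which weeks goal-setting counts as observed.
2. **Discussion.** Delete the statement of sufficient power for mediators, or restate it for the within-arm analysis.
3. **Optional.** If between-arm mediation is still wanted, explore the norms and behavioral control items, which all arms answer. Use their three-month values against binge drinking days at six and nine months, adjusted for baseline values of mediator and outcome. This answers a different and narrower question. Each is a single item, the norms item partly reflects the respondent's own drinking, and behavioral control is not among the targets named in the SA+F intervention section.

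The first two changes cost wording only and need no new data. The price is giving up any statement on how much of the arm effect runs through intention or goals, which the planned data could not supply in any case.

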## Discussion

The TRAC study is the first large-scale randomized trial to examine the effectiveness of a text message program for initiating and maintaining reductions in binge drinking among at-risk young adults. If found to be effective, our intervention could be easily scaled-up as a stand-alone program to provide widespread support with minimal disruption to normal clinical practice. Additionally, it could easily be included as a piece in a multi-component intervention, such as a “booster” to traditional in-person counseling interventions. By incorporating longitudinal assessments of drinking behavior in a patient’s natural environment through SMS, stepped-care models could be built where individuals who continue to report hazardous use after program exposure could then be referred directly to a help line or counselor.

There are several potential strengths of our research design worth mentioning. In addition to being large enough to demonstrate reductions in alcohol consumption immediately following intervention (three-month follow-up) as well six months later (nine-month follow-up), we have sufficient power to examine mediators of change associated with this intervention. Inclusion of an assessment-only group minimizes the potential for assessment effects to bias estimates of intervention efficacy. While all participants complete informed consent, where we outline the various treatments they may be subjected to, we do not specifically tell them which one. We believe that this may reduce expectation biases. All baseline measures and outcomes are reported to an automated computer system, potentially increase disclosure of potentially sensitive or embarrassing information, thus reducing reporting biases. By collecting pre-weekend drinking intentions/plans, goal-setting/plan changes, and post-weekend consumption in the intervention group, we will be able to examine “micro processes” or mechanisms of change not previously available in brief intervention studies. Finally, we have made efforts to design our mobile intervention both from a theory-driven approach to behavior change [44] and a user-centered approach [45], which will serve the dual purposes of increasing potential effectiveness as well as reducing intervention attrition.

The major methodological challenge in this study relates to retention of participants. ED-based brief intervention studies may have lost to follow-up rates as high as 40% [19]. Accordingly, we have adopted a method of obtaining multiple points of contact from participants, conducting follow-up through a web-based platform, and analytic methods for estimating the degree of any attrition bias and potentially adjusting for it. If we are able to meet these challenges, we will generate data about a mobile behavioral program that has the potential to improve the health of young adults outside of traditional care settings.

## Trial status

Active recruitment
